##### Workshop 2- motivation and anti-doping

Workshop 2 was designed by the Australian and United Kingdom teams. At the beginning of the second workshop, successes and pitfalls in implementing the taught material from the first workshop are discussed. In addition, reflective diaries are reviewed, and further advice is offered as coaches problem solve together to overcome obstacles in implementation. Following this activity, the main aims of Workshop 2 are to:

•Increase coaches’ knowledge of anti-doping rules and regulations and raise their awareness of the tools available to reduce the risk of inadvertent doping.•Upskill coaches in how to apply need supportive communication, drawing from motivational principles outlined in Workshop 1, to reduce athletes’ willingness to dope and risk of inadvertent doping.

The material of Workshop 2 is specific to doping in terms of showing how motivational strategies can support or undermine doping-related variables at the athlete level. For example, coaches are trained to become more aware of how psychologically controlling tactics and pressuring techniques that focus on success at any costs can push athletes to use prohibited substances in an effort to appease their coach and gain their approval. It is also discussed how need thwarting coach environments can make athletes more susceptible to inadvertent doping because of increased adeptness at taking risks to gain coach approval. In contrast, it is shown how fostering athletes’ initiative, acknowledging their negative emotions, and offering unconditional support can prevent the development of contingencies in the athlete-coach relationship. Hence, under such circumstances athletes are less likely to resort to doping use as means of validating their self-worth and proving themselves to their coach, and are less susceptible to inadvertent doping. Such adaptive and maladaptive motivational strategies, and many other similar examples, are incorporated into our coach education program to help coaches self-reflect on their own motivational strategies and critically appraise how they influence their athletes’ willingness to take potentially illegal substances.

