The training material helps coaches share existing anti-doping resources and communicate about doping with their athletes in a more need supportive manner and less need thwarting manner, using some of the aforementioned strategies. For example, emphasis is placed on providing rationales, acknowledging anxieties or uncertainties, being responsive to questions, taking time to listen to athletes’ opinions, and avoiding personal attacks, imposed goals, or intimidating tactics (see Ntoumanis et al., 2018). Given the influential role of peers on doping-decision making aspects (e.g., Woolf et al., 2014), coaches are trained to instigate such discussions both individually and in groups of athletes, so that athletes can also be educated as to how their communications and interactions with fellow athletes can influence doping-related outcomes.

Both experimental workshops use an interactive approach where coaches are encouraged to ask questions and discuss content amongst fellow participants and with the presenters. There are a number of activities included in the design of the experimental workshops which invite participants to actively participate. For instance, coaches are invited to write down on sticky notes what they might perceive to be some of the reasons athletes might want to be ‘clean,’ that is not use prohibited substances. They are then provided with an A3 laminated ‘motivation barometer’ (**Figure 1**) and asked to place the sticky note in a position on the barometer that best suits the identified reasons. Other activities involve discussions of videos, role playing of a hypothetical coach-athlete interaction, and group activities which aim to apply theoretical principles to specific sport situations (e.g., discuss the application of need supportive strategies in situations where a coach is approached by an athlete who wants to use nutritional supplements to speed up their strength recovery from an injury).

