**FIGURE 2 F2:**
[figure not shown]
Workbook examples.

•Content from the presentation slides with questions to check understanding and summaries of main points.•Descriptions of the practical activities run in the workshops.•A personal action plan for coaches to implement the motivational strategies taught in the workshops. We created action and coping planning sheets for coaches to think through how/when strategies might be used, what challenges they might face in doing so, and how these challenges can be overcome.•Instructions on a week-by-week basis regarding the practicalities of implementing motivational strategies when communicating with athletes. Detailed descriptions are given on how to implement these strategies before, during, or after training. Coaches can keep a reflective diary of success and failures in implementing in their coaching sessions what they have learned at the workshops.

The workbooks are designed to be portable to allow coaches to carry them during training sessions and to take notes. The coaches are encouraged to utilize the workbooks throughout the program.

The project teams have also created restricted access Facebook groups for participating coaches in the experimental condition in each country. The Facebook groups provide coaches with the opportunity to engage in discussions with the project team and interact with fellow coaches participating in the program. For coaches not on Facebook, they receive a weekly email communication from the project team. The team provides weekly prompts via Facebook or email to remind coaches to continue to implement the strategies taught during the workshops, as outlined in their workbooks. In addition, the groups are used to disseminate topical information, including research publications, news articles, and videos illustrating different motivational strategies/communication styles by coaches. We have also created videos with amateur actors depicting different styles of coach communication. These video clips are designed to assist the coaches to grasp the motivational concepts discussed during the workshops. The coach actors in the video clips reinforce to the athlete actors the importance of providing accurate information about the risks of supplement use. However, different video clips have been created (each about 5 min long) in which a coach is interacting with an athlete in need supportive, need thwarting, or motivationally neutral ways.

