### Piloting of the Material

Pilot deliveries of the intervention workshops have been conducted across all three countries using between 5 and 7 coaches of varying experience. Following the workshops, coaches were invited to provide feedback via evaluation questionnaires. During these workshops, coaches were able to provide comments on the general workshop approach/delivery in addition to the specific interactive activities and material that we prepared. The feedback has been very positive and will be presented in a future process evaluation publication.

### Phase 2

In this phase, we are currently delivering a cluster randomized control trial in Australia, United Kingdom, and Greece. This study is a parallel group, two-condition, superiority trial. Due to calendar differences in the start of sport seasons, the intervention started half a year earlier in Australia than in the other two countries. Recruitment is ongoing in Greece and the United Kingdom and has been completed in Australia, hence the description of the methodology in this section is written in future tense.

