#### Participants and Recruitment

We will recruit from sport clubs 20 full-time or part-time coaches in each condition from each country, giving a total sample size of 120 coaches and estimated 1200 athletes. There are no exclusion criteria for coaches based on their own demographic or coach history characteristics. Inclusion criteria include having a minimum of six athletes who are 14 years or older, train at least once a week, and compete on a regular basis. No more than six coaches will be recruited from any given club, and coaches within that club will be allocated to the same condition. Due to the number of recruited participants, we will use a staggered recruitment design. We will aim to recruit from a variety of sports in all three countries, and from both male and female coach and athlete samples. Power estimates have been calculated with the Optimal Design Software (Spybrook et al., 2011) for clustered RCTs with treatment at level 2, primary outcomes at level 1, estimated average number of athletes per coach to be 10, intraclass correlation coefficient of 0.005, small effect size (δ =0.22) for willing to engage in doping, and oversampling by about 30% to counter possible missing values and coach/athlete dropout from the study. Clubs will be assigned randomly to either a control or intervention condition with a 1:1 allocation using permuted blocks of random sizes. The block sizes will not be disclosed to ensure concealment. A researcher will carry out randomization (and allocate clubs to the two arms) via a computer software following recruitment. Allocation concealment will be ensured, as randomization will not be disclosed until after the intervention starts. All research assistants who will collect data will be blind to condition allocation. There will be no circumstances in which unblinding for those individuals will be necessary. Due to the nature of the intervention, participants cannot be blinded to allocation, but they will be strongly encouraged not to discuss the content of their training with coaches from other sport clubs until after the end of the program.

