The workshops will be delivered by our research team members who have expertise in psychology and experience in delivering workshops about motivation or anti-doping to coaches and athletes. To standardize the delivery of the workshops across countries, presenters at the workshops will be trained using video recorded demonstration workshops and detailed slide notes. The workshops will take place in a prearranged central location with access to suitable teaching facilities (i.e., close seating arrangements, projector). These locations include university campuses, local sport and recreation departments, or at participating sporting clubs or organizations.

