### Analyses

The main statistical analyses of the questionnaire data will involve multilevel modeling, accounting for both the longitudinal and nested (athletes within coaches) nature of the data. Country differences will be tested with contrast effects within multilevel modeling. Data from those who dropout from the study will be included in the analyses using intention-to-treat principles. We will compare the results obtained from these analyses with those obtained from a “per protocol analysis” (i.e., excluding participants who dropped out). In terms of missing data, results will be compared using imputation methods and multilevel modeling methods for handling such data. Analysis of the role-playing videos for fidelity assessments will involve repeated-measures MANOVAs. Interviews will be analyzed thematically, within and across countries, by using deductive and inductive approaches to identify patterns in the data (Braun and Clarke, 2006).

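### The experimental workshops train coaches in groups, but the stated model treats coaches as independent, so standard errors may be too small if sessions differ

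*Protocol article*

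**What the plan says.** The Analyses section of the Protocol article sets out the main questionnaire analysis as multilevel modelling "accounting for both the longitudinal and nested (athletes within coaches) nature of the data". The power calculation under Participants and Recruitment has the same two levels: treatment at level 2 (the coach) and the primary outcome at level 1 (the athlete), with 10 athletes per coach and an ICC of 0.005. Neither place names a workshop session or a club.

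The same article describes delivery to groups. In the second experimental workshop, "further advice is offered as coaches problem solve together to overcome obstacles in implementation". In both experimental workshops, "coaches are encouraged to ask questions and discuss content amongst fellow participants and with the presenters". The Procedure section says "The workshops will take place in a prearranged central location" and lists university campuses, local recreation departments and participating clubs or organisations as venues, so a session can mix clubs or hold coaches from one club only. Under Participants and Recruitment, "we will use a staggered recruitment design", which implies several sessions over time. The number of sessions and the coaches per session are not given. The only group size stated is for the pilots, "using between 5 and 7 coaches of varying experience".

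Participants and Recruitment also makes the club the unit of randomisation, with up to six coaches per club, all in the same arm.

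**The concern.** Coaches in one session share a presenter, a peer group and a start date. If these affect how well coaches take up the training, then coaches from the same session, and their athletes, are more alike than coaches from different sessions. This variation enters the arm contrast divided by the number of sessions, which is smaller than the number of coaches. A model that stops at the coach divides it by the number of coaches, so its standard error is too small and its confidence intervals too short.

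The primary outcome (athletes' willingness to take potentially banned substances) is exposed indirectly, through the coach. Coach outcomes, such as efficacy to discuss doping, are exposed directly. A club level alone would not remove the problem where a session mixes clubs.

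**Working it through.** **Inputs from the article (Participants and Recruitment):** 120 coaches, m = 10 athletes per coach, ICC ρ = 0.005, effect 0.22 SD, about 30% oversampling.

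**Assumptions:** two-sided 5% test; k = 6 coaches per session, with 10 as an upper case; session ICC ρs of 0.0025 or 0.005. All athletes of one coach share that coach's session, so session variance is part of between-coach variance. Holding the total at 0.005 therefore means ρs cannot exceed 0.005.

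**1. The plan's own figure.** Alpha and power are not stated. At two-sided 5% and 90% power, 2 × (1.960 + 1.282)² / 0.22² gives 435 athletes per arm. The design effect is 1 + 9 × 0.005 = 1.045, and 435 × 1.045 = 454.6 athletes, or 46 coaches per arm and 92 in all. Then 92 × 1.3 = 119.6, which matches 120. The total is thus consistent with a two-level calculation and contains no allowance for correlation between coaches.

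**2. Adding sessions.** The design effect in the stated model is D0 = 1 + (m − 1)ρ = 1.045. With session correlation in both arms it is D = D0 + m(k − 1)ρs. If only intervention sessions vary, it is the average of D0 and D. The true standard error is √(D/D0) times the reported one, and the true type I error is 2 × [1 − Φ(1.96 / √(D/D0))].

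Example, k = 6 and ρs = 0.0025, both arms: D = 1.045 + 10 × 5 × 0.0025 = 1.170; ratio √(1.170/1.045) = 1.058; true error 2 × [1 − Φ(1.852)] = 6.4%.

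| k | ρs | Sessions vary in | D | SE ratio | True type I error |
|---|---|---|---|---|---|
| 6 | 0 | – | 1.045 | 1.00 | 5.0% |
| 6 | 0.0025 | intervention only | 1.108 | 1.03 | 5.7% |
| 6 | 0.005 | intervention only | 1.170 | 1.06 | 6.4% |
| 6 | 0.0025 | both arms | 1.170 | 1.06 | 6.4% |
| 6 | 0.005 | both arms | 1.295 | 1.11 | 7.8% |
| 10 | 0.005 | intervention only | 1.270 | 1.10 | 7.5% |
| 10 | 0.005 | both arms | 1.495 | 1.20 | 10.1% |

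Simulation of t-tests on coach means agrees to within a few tenths of a point; for k = 6, ρs = 0.005, intervention only, it gave 6.5%.

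**3. Power.** With 92 analysed coaches (460 athletes per arm) and a correct standard error, power is Φ(0.22 / √(2D/460) − 1.96). It is 0.904 at D = 1.045, 0.870 at 1.170, 0.834 at 1.295 and 0.779 at 1.495.

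**4. Coach outcomes.** One value per coach gives D = 1 + (k − 1)ρs against 1. The planning ICC does not limit ρs here. For k = 6, both arms, and illustrative ρs of 0.02, 0.05 and 0.10: D = 1.10, 1.25 and 1.50, and the true error is about 6.2%, 8.0% and 11.0%.

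**The case against.** The strongest reply is that the size is unknown and may be nil. The article gives no session size, number of sessions or session ICC, and the Procedure section standardises delivery through video demonstrations and detailed slide notes, which should reduce differences between presenters. This stands: the point is conditional on positive session variance.

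The interactive format is documented for the experimental workshops only; the control arm has a single one-hour information session. The intervention-only figures are therefore the better supported ones. Where a session holds coaches from one club only, a club level would already absorb session variation, and the article does not say how often sessions mix clubs. Both limits stand.

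An article condenses a fuller plan, which could add levels. That is fair as far as omissions go, but here the article states the nesting in the analysis and uses the same two levels in the power calculation. The criticism is of a stated structure.

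Two stronger readings are tempting. A reader might infer error rates of 14% to 22% for athlete outcomes. Those need session ICCs of 0.01 to 0.02 with 10 coaches per session in both arms, added to the coach ICC of 0.005. Athletes of one coach would then correlate at 0.015 to 0.025, three to five times the planning value. A reader might also count the online groups as a further reason for a session term. They are described as "restricted access Facebook groups for participating coaches in the experimental condition in each country": one per country and in one arm only. They are not sessions, and a session effect would not capture them.

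**Conclusion.** The point holds in conditional form. Group delivery is documented and the stated model stops at the coach, so any positive session variance not absorbed elsewhere makes the standard error of the arm contrast too small. The documents do not show that it *is* too small.

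Within the plan's own ICC of 0.005 and with 6 coaches per session, the effect on the primary outcome is modest: a true type I error of about 5.7% to 6.5% if only intervention sessions vary and 6.4% to 7.8% if both arms vary, against an assumed nominal 5%. About 10% is the upper case (10 per session, both arms, all between-coach variance at session level). Coach outcomes are more directly exposed, but the article gives no ICC from which to size the effect.

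**What to change.** - Record the workshop session each coach is scheduled for and the one attended, in both arms, and for each of the two experimental workshops. The scheduled session keeps non-attenders in an intention-to-treat model.
- Include club, the randomised unit, as a level above coach.
- Add session as a random effect in the athlete and coach models, crossed with club where sessions mix clubs, with a variance allowed to differ by arm and small-sample degrees of freedom.
- If there are too few sessions for a stable variance estimate, pre-specify a sensitivity analysis with session-clustered, small-sample-corrected standard errors instead.

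The cost is an attendance log, extra model terms and somewhat wider confidence intervals. The log should be kept as workshops are delivered, since session membership may be impossible to reconstruct later.

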##### Fidelity assessment

Coaches are also asked to participate in a semi-structured role play. During the role play, a trained research assistant plays the role of an athlete considering taking banned substances while the coach responds in ways which they would consider as a typical response from them. In this hypothetical scenario, a 23-year-old athlete has experienced a performance ‘plateau’ in that they haven’t seen their performance improve over the last 12 months. They are considering taking performance enhancing supplements to break this trend. The role play typically lasts about 20 min and takes place on two occasions, before the intervention and after the end of it, as indicated in **Table 1**. The role plays are audio recorded so that they can be coded later on in terms of the communication style used by the coach. We will use an observational scale (Quested et al., under review) with trained raters, blinded to the experimental condition, to rate the frequency and intensity of need supportive and need-thwarting communication used in these discussions. The aim of this assessment is to establish whether the intervention arm coaches’ communication during the second role play demonstrates fidelity to the intervention (i.e., “treatment enactment”; see Borrelli, 2011), and also to compare the ratings of the coaches in the two arms at each time point. A more rigorous test would have been to code actual communications between coaches and their athletes, however, this was not feasible due to resource constraints as well as the logistical and ethical challenges of filming such discussions. Our role playing is, hence, a proxy measure of fidelity to treatment enactment. We have followed many of Borrelli’s recommendations to enhance fidelity throughout the research process including study design (e.g., explicit use of a theoretical model, pilot testing, and feedback from participants), training (standardized training, accommodate learner differences, assess skill acquisition, and prevent skills drift), treatment delivery (interviews at the end of the project, use of a manual), and treatment receipt (e.g., present material in an engaging way, assess confidence to apply the skills delivered).

### Phase 3

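### The between-arm comparison of coach role-play ratings is assigned to repeated-measures MANOVA, which makes no allowance for the randomised club that up to six coaches can share

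*Protocol article*

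**What the plan says.** Randomisation is by club (Participants and Recruitment): "Clubs will be assigned randomly to either a control or intervention condition with a 1:1 allocation using permuted blocks of random sizes". Several coaches may come from one club: "No more than six coaches will be recruited from any given club, and coaches within that club will be allocated to the same condition". The target is 20 coaches per condition in each of three countries, "giving a total sample size of 120 coaches and estimated 1200 athletes".

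The role play (Fidelity assessment) "takes place on two occasions, before the intervention and after the end of it". One aim is to see whether trained coaches enact the training. The other is "to compare the ratings of the coaches in the two arms at each time point", so a between-arm comparison is planned.

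The Analyses section assigns multilevel modelling to the questionnaire data, "accounting for both the longitudinal and nested (athletes within coaches) nature of the data". The role play gets a different method: "Analysis of the role-playing videos for fidelity assessments will involve repeated-measures MANOVAs". No club term or cluster adjustment is named for it. The same section says "Data from those who dropout from the study will be included in the analyses using intention-to-treat principles" and adds that imputation and multilevel approaches to missing data will be compared. It does not say whether those two statements extend to the role play.

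**The concern.** A repeated-measures MANOVA accounts for the correlation between a coach's two occasions and between the ratings. It does not account for correlation between coaches of the same club. Because all coaches in a club share an arm, that correlation inflates the variance of the arm difference, and an analysis that ignores it reports standard errors that are too small. Such correlation is plausible: workshops may be held at participating clubs, and intervention coaches work through implementation problems together.

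The test at stake is that of the first coach hypothesis, that trained coaches use more need support and less need thwarting when they talk about doping. None of the seven coach questionnaires records the style used; the fourth asks how effective each style is thought to be. The athlete-rated scale covers coach behaviour in general, not doping discussions. The role play is therefore the only listed measure for this hypothesis, and a false-positive rate above the nominal level bears directly on it.

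**Working it through.** **The plan's own figure.** No sample size is given for the role play. The 120 coaches come from the athlete primary outcome. Inputs from Participants and Recruitment: δ = 0.22, 10 athletes per coach, intraclass correlation 0.005, about 30% oversampling. Assumed, because not stated: two-sided 5% and 90% power.

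- Per arm, unclustered: 2 × (1.960 + 1.282)² / 0.22² → 435 athletes.
- Design effect: 1 + (10 − 1) × 0.005 = 1.045.
- Coaches per arm: 435 × 1.045 / 10 = 45.5 → 46, so 92 in total; 92 × 1.3 = 119.6.

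The figure of 120 reproduces on those assumptions and is not in dispute. The 0.005 refers to athletes within a coach and says nothing about coaches within a club.

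**Effect of ignoring club.** Let m be coaches per club (1 to 6; the mean is not stated) and ICC the within-club correlation of the quantity tested (not stated, so assumed).

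- Design effect: DE = 1 + (m − 1) × ICC.
- Effective number of coaches: 120 / DE.
- True error rate of a nominal 5% test of one rating: 2 × [1 − Φ(1.96 / √DE)].

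Example, m = 3 and ICC = 0.20: DE = 1.40; 120 / 1.40 = 85.7; 1.96 / √1.40 = 1.656; error rate 9.8%.

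The last column simulates the group-by-time MANOVA on two change scores. It used 120 coaches and 4000 runs per setting, with an assumed correlation of −0.4 between the two ratings and the ICC applied to the change scores.

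| Coaches per club | ICC (assumed) | DE | Effective coaches | True alpha, one rating | Simulated alpha, two-rating MANOVA |
|---|---|---|---|---|---|
| 2 | 0.05 | 1.05 | 114.3 | 5.6% | 6.3% |
| 2 | 0.10 | 1.10 | 109.1 | 6.2% | 6.6% |
| 2 | 0.20 | 1.20 | 100.0 | 7.4% | 7.9% |
| 3 | 0.05 | 1.10 | 109.1 | 6.2% | 7.5% |
| 3 | 0.10 | 1.20 | 100.0 | 7.4% | 8.8% |
| 3 | 0.20 | 1.40 | 85.7 | 9.8% | 11.7% |
| 6 | 0.05 | 1.25 | 96.0 | 8.0% | 8.9% |
| 6 | 0.10 | 1.50 | 80.0 | 11.0% | 14.2% |
| 6 | 0.20 | 2.00 | 60.0 | 16.6% | 23.4% |

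With one coach per club, or with ICC = 0, DE is 1 and there is no inflation; the simulation gave 4.5–5.5% in those settings. At ICC = 0.01 the formula gives 5.1% with two coaches per club and 5.6% with six.

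**Missing second role plays.** By default a repeated-measures MANOVA keeps only coaches with both occasions. The article gives no rate for this loss. An assumed 10%, 20% or 30% would leave 108, 96 or 84 of 120 coaches.

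**The case against.** The strongest reply is that the role play is described as a proxy for fidelity and is not the primary outcome, and that the size of the problem rests on two quantities the article does not give. Six coaches per club is a recruitment ceiling. If most clubs supply one or two coaches, inflation is nil or modest. All of this stands. It limits the size but does not remove the mismatch, because the article permits clubs with several coaches, plans a comparison of arms, and names a method that ignores club.

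Several stronger readings are tempting, and the documents do not support them:

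- **Coaches without a second role play are deleted.** The article does not say so. Its Analyses section includes dropouts and names imputation, and a MANOVA can be run on imputed data. Only the conditional statement holds.
- **The 30% oversampling gives the coach loss.** That allowance combines missing values with coach and athlete dropout, for an athlete outcome. It is not a rate of missed role plays.
- **The test carries the claimed mechanism.** Under Hypotheses, the manipulation check is athletes' perceptions of their coach and the mediator is athletes' need satisfaction and frustration. Both are athlete-reported.
- **A baseline significance test is planned.** Comparing ratings at each time point does not state one, and a group-by-time analysis does use the baseline.
- **The coach questionnaires are analysed wrongly.** The article names only athletes within coaches as nesting and does not give the levels for coach outcomes. An error there would be inferred from silence.

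**Conclusion.** The point holds in a limited form. As written, the between-arm test of the role-play ratings ignores the unit of randomisation and is anti-conservative wherever clubs supply several coaches whose ratings correlate. For an assumed within-club correlation of 0.05 to 0.20, true alpha per rating is about 5.6–7.4% at two coaches per club, 6.2–9.8% at three and 8.0–16.6% only if every club is at the ceiling of six. The joint two-rating test is somewhat worse under the same assumptions. How a missing second role play will be handled is unclear; a default complete-pairs MANOVA would conflict with the stated intention-to-treat principle. The consequence is confined to the first coach hypothesis and the fidelity comparison. The primary athlete analysis and the mediation test do not depend on this MANOVA. The change should be made, but the trial's main conclusion does not rest on it.

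**What to change.** Replace the MANOVA with a linear mixed model for each rating (need support, need thwarting) on all randomised coaches. Include a random intercept for club, with the baseline rating, country and arm as fixed terms. Name the arm contrast at the second role play as the test.

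Say how coaches without a second role play stay in the analysis. One option is multiple imputation that respects club. The other is to model both occasions jointly, with a club term that may differ by occasion. If clubs turn out to be few (120 / 6 = 20 at the extreme), use a small-sample degrees-of-freedom correction.

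State the same coaches-within-clubs structure for the coach questionnaire outcomes, so that all coach-level tests respect the randomised unit.

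The cost is a change of analysis wording and wider intervals, by a factor of √DE. On the assumed correlations that is about 1.02–1.10 at two coaches per club, 1.05–1.18 at three and 1.12–1.41 at six. Adjusting for the baseline rating may recover part of this. No data collection changes, and the primary athlete outcome is untouched.
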